## Abstract

**Background:**

Diet is among the most influential lifestyle factors impacting chronic disease risk. Nutrimetabolomics, the application of metabolomics to nutrition research, allows for the detection of food-specific compounds (FSCs) that can be used to connect dietary patterns, such as a Mediterranean-style (MED) diet, to health. This validation study is based upon analyses from a controlled feeding MED intervention, where our team identified FSCs from eight foods that can be detected in biospecimens after consumption and may therefore serve as food intake biomarkers.

**Methods:**

Individuals with overweight/obesity who do not habitually consume a MED dietary pattern will complete a 16-week randomized, multi-intervention, semi-controlled feeding study of isocaloric dietary interventions: (1) MED-amplified dietary pattern, containing 500 kcal/day from eight MED target foods: avocado, basil, cherry, chickpea, oat, red bell pepper, walnut, and a protein source (alternating between salmon or unprocessed, lean beef), and (2) habitual/Western dietary pattern, containing 500 kcal/day from six non-MED target foods: cheesecake, chocolate frozen yogurt, refined grain bread, sour cream, white potato, and unprocessed, lean beef. After a 2-week washout, participants complete four, 4-week intervention periods, with biospecimen sampling and outcome assessments at baseline and at intervention weeks 4, 8, 12, and 16. The primary outcome is change in the relative abundance of FSCs from the eight MED target foods in participant biospecimens from baseline to the end of each intervention period. Secondary outcomes include mean change in cardiometabolic health indicators, inflammatory markers, and adipokines. Exploratory outcomes include change in diversity and community composition of the gut microbiota.

**Discussion:**

Our stepwise strategy, beginning with identification of FSCs in whole diets and biospecimens, followed by relating these to health indicators will lead to improved methodology for assessment of dietary patterns and a better understanding of the relationship between food and health. This study will serve as a first step toward validating candidate food intake biomarkers and allow for assessment of relationships with cardiometabolic health. The identification of food intake biomarkers is critical to future research and has implications spanning health promotion and disease prevention for many chronic conditions.

**Trial registration:**

Registered at ClinicalTrials.gov: NCT05500976; Date of registration: August 15, 2022.

## Administrative information

Note: the numbers in curly brackets in this protocol refer to SPIRIT checklist item numbers. The order of the items has been modified to group similar items (see http://www.equator-network.org/reporting-guidelines/spirit-2013-statement-defining-standard-protocol-items-for-clinical-trials/).

## Introduction

### Background and rationale {6a}

The sustained modification of diet provides perhaps the single most important opportunity to influence an individual’s health throughout their lifetime. Consistent findings demonstrate consumption of fruits, vegetables, legumes, nuts, whole grains, and seafood within healthy dietary patterns such as a Mediterranean-style (MED) dietary pattern has several health benefits and may contribute to reducing risk factors for cardiometabolic disease and increasing longevity [1, 2]. Great efforts have been made to test the effectiveness of isolated nutrients and phytochemicals from dietary patterns such as MED as well as specific foods consumed within complex background diets [3]. However, weak and often inconclusive findings connecting specific dietary intakes to health outcomes are frequently observed and could be due to the heterogeneity of study designs, lack of high quality randomized controlled trials in nutrition research, variations in dosage and timing of interventions, limitations of dietary assessment methodologies, or complexity of dietary patterns, among others [4–7]. It could also be that multifaceted interactions of foods and food metabolites, rather than individual nutrients or compounds, are required for health benefits. Hence, to improve our understanding of the relationship between diet and health, a step-wise strategy is warranted, beginning with identifying compounds that are unique to specific foods in biospecimens followed by determining associations between these signatures, dietary intakes, and health [8–10].

Our group has employed such a strategy to identify food-specific compounds (FSCs) that are detected in biospecimens, associate with intake of that food, and are associated with cardiometabolic health indicators [11–13]. Our findings suggest that several foods consumed within complex healthy dietary patterns such as the Dietary Approaches to Stop Hypertension (DASH) and MED diets have novel food-specific signatures [11–13]. To date, we have conducted metabolomics analyses of over 100 foods to identify compounds uniquely present in these foods. Using the established platform and methodology developed by our team [14, 15], we have identified thousands of distinct compounds within individual foods present in a MED dietary pattern [16], demonstrating our ability to use our approach to define FSCs and suggesting these FSCs may be further explored as biomarkers of food intake. The relationships between these biomarkers of food intake and health effects can then elucidated.

In addition to identifying FSCs from individual foods, we have shown that these compounds are present in biospecimens such as blood and urine from individuals who have consumed these foods as part of a fully controlled feeding intervention [11, 13]. These results suggest FSCs are discernable in biospecimens after consumption of complex meals within overall dietary patterns and thus may be useful as putative biomarkers of food intake [17]. We have also demonstrated the ability to link observed FSCs in plasma with clinical indicators, suggesting food compounds may be associated with a biologic effect (i.e., putative biomarkers of effect) [11]. For example, the MED intervention improved participant systolic and diastolic blood pressures, and plasma/serum total cholesterol, triglycerides, and LDL cholesterol [16]. Results from our analyses identified FSCs that are associated with improvement in one or more of these cardiometabolic health indicators. These promising results warrant follow-up to confirm findings in an independent cohort.

Our results support the use of unmetabolized FSCs in either plasma or urine as candidate biomarkers of food intake. However, evaluation of multiple biospecimen types (e.g., blood and urine) simultaneously may increase coverage by collecting complementary information about different aspects of food metabolism [18]. Thus, collection and analysis of multiple biospecimen types will provide more comprehensive compound lists to define metabolomic signatures for testing associations with health indicators. Our preliminary results need to be prospectively tested within an independent intervention, a necessary next step for evaluation of reproducibilty and potential validation as biomarkers of food intake. Notably, our previous nutrimetabolomics research has been conducted within fully controlled feeding trials, making it difficult to elucidate the effects of incremental shifts between an “unhealthy” habitual/Western dietary pattern toward “healthy” evidence-based dietary patterns such as DASH or MED. The current mini-MED clinical trial study design and extensive biospecimen sampling plan directly address these limitations.

We are conducting a 16-week randomized, multi-intervention, semi-controlled feeding study among individuals with overweight/obesity who do not habitually consume a MED dietary pattern to comprehensively evaluate the reproducibility of FSCs using our innovative nutrimetabolomics approach. The novel FSCs identified in our eight MED target foods will be evaluated in participant biospecimens to assess change after intervention and to validate associations with cardiometabolic health indicators in this prospective semi-controlled feeding trial. The overall scientific premise is that FSCs will be reproducibly found when individuals consume specific foods, will not be found when individuals do not consume those foods, and will be associated with beneficial indicators of cardiometabolic health. In addition, we will evaluate the reproducibility of FSCs from beef in the context of different backgrounds (MED vs habitual/Western foods). Based upon existing literature, exploratory analyses will also be conducted to identify shifts in microbiome structure/function in response to incremental dietary changes.

### Objectives {7}

The primary aim of the study is to validate results from metabolomics analyses of foods and biospecimens from a completed MED-style dietary intervention in a prospective feeding trial. Our primary hypothesis is that pre-defined FSCs in participant biospecimens will be responsive to dietary intakes and reproducible within individuals over time, with beef FSCs stable and reproducible within the context of different dietary backgrounds (i.e., the MED and Western dietary patterns). Our secondary aims are to evaluate impacts of incremental changes in diet on cardiometabolic health indicators and microbiome structure and function. Our secondary hypotheses are that a Mediterranean-amplified dietary pattern will lead to improvements in cardiometabolic health indicators and beneficial changes in gut microbiome diversity and community composition over time and compared to a habitual/Western-style dietary pattern.

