#### Sample size {14}

Most of our planned analyses use each individual as their own control by looking at the change over each dietary intervention period. This reduces between subject variability compared to a cross-sectional analysis and increases the statistical power at a given sample size. To obtain a reasonable minimum expected effect size for the mean difference divided by the standard deviation of the difference (i.e., Cohen’s *d* effect size), we used our analysis of salmon FSCs [13]. The minimum salmon FSC effect size that passed an FDR adjustment was 0.45. Using a paired *t*-test after consuming the food, a sample size of *N* = 20 was needed to achieve 80% power for this effect size of 0.45 and a Bonferroni multiple testing adjustment for the number of compounds that increased in the preliminary MED data (*N*_compounds_ = 21; *p*-value_adjusted_ = 0.05/21 = 0.0024). We assume a 10% loss to follow-up based on our experience in similar dietary intervention trials and therefore enroll *n* = 22 eligible individuals to have *n* = 20 individuals complete the trial.

We also evaluated the power of *N* = 20 sample size further using the Bonferroni adjustment for the 21 compounds that increased after consumption of the preliminary Mediterranean diet foods (*p*_adj_ = 0.0024) and a stricter adjustment using all 355 compounds that were detected in the MED foods and plasma (*p*_adj_ = 0.05/355 = 0.00014). For both significance thresholds, we achieve power across a range of relevant effect sizes (Fig. 2) including nearly 100% power to detect an effect size of 0.75 (the median effect size for the salmon FSCs that passed the FDR threshold).

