### Assignment of interventions: allocation

#### Sequence generation {16a}

All participants complete the mini-MED and Western dietary interventions twice each for four total intervention periods. Participants are randomized (1:1) to start either the mini-MED or Western dietary interventions, with subsequent assignment to the other upon completion of the first. A second randomization within the mini-MED arm is conducted to allocate participants to order of consumption of either salmon or lean, unprocessed beef as a protein source resulting in a total of four possible intervention orders (Fig. 1). Lean, unprocessed beef is consumed as the protein source in both Western intervention periods. A permuted block randomization scheme and stratification by sex has been generated and is utilized to ensure balance between intervention order and number of males and females. The allocation sequence was generated using computer-generated random number sequence in R using the *sample* command in *base* R package.

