## Statistical methods

### Statistical methods for primary and secondary outcomes {20a}

Assessment of the primary outcome of change in FSCs will be completed using the intercept of linear mixed effects models (LMMs) with change in FSCs (post–pre) as the outcome and a random intercept to control for repeated measures. Analysis will be stratified by mini-MED and Western interventions since we expect FSCs to increase during the mini-MED arm and to decrease during the Western arm. FSCs that significantly increase during the mini-MED interventions and significantly decrease during the Western interventions will be considered validated. We will adjust for multiple testing using false discovery rate (FDR) for the number of FSCs [37]. We will complete stratified analysis by intervention period to assess reproducibility of FSCs in increase (mini-MED) and decrease (Western). The relationship between cardiometabolic health indicators and diet intervention will be assessed using LMMs similar to that described above. The relationship between cardiometabolic health indicators and FSCs will be assessed using LMMs over all intervention periods with an interaction term for FSCs and diet (i.e., mini-MED, Western) to capture differential effects by diet.

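### The primary hypothesis says beef compounds are stable across Mediterranean and Western backgrounds, but no planned analysis of the compounds can support stability

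*Protocol article*

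**What the plan says.** Objectives {7} makes stability part of the primary hypothesis: FSCs should be responsive and reproducible, "with beef FSCs stable and reproducible within the context of different dietary backgrounds", namely the Mediterranean and Western patterns. Background and rationale {6a} gives the same aim as reproducibility: "we will evaluate the reproducibility of FSCs from beef in the context of different backgrounds (MED vs habitual/Western foods").

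The design serves that aim. Each participant eats beef in one of the two mini-MED periods, and under Sequence generation {16a} "Lean, unprocessed beef is consumed as the protein source in both Western intervention periods".

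Statistical methods {20a} analyses FSCs "using the intercept of linear mixed effects models (LMMs) with change in FSCs (post–pre) as the outcome", separately for mini-MED and Western. It expects increases on the first and decreases on the second, with no exception for beef. The decision rule is: "FSCs that significantly increase during the mini-MED interventions and significantly decrease during the Western interventions will be considered validated". Multiplicity is handled thus: "We will adjust for multiple testing using false discovery rate (FDR) for the number of FSCs". Reproducibility is the same analysis split by period: "We will complete stratified analysis by intervention period to assess reproducibility of FSCs in increase (mini-MED) and decrease (Western").

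The one FSC-by-diet interaction in that section concerns association with cardiometabolic indicators. The additional analyses {20b} are by covariates such as age, sex and baseline value. Sample size {14} addresses detection of change only.

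**The concern.** Stability across two backgrounds is a claim that no relevant difference exists. It needs an estimate of the difference and a tolerance to judge it by. Every FSC test printed here asks instead whether a mean change differs from zero, and the only rule for a positive conclusion requires a significant rise on one diet and a significant fall on the other. Mini-MED beef and Western are never compared directly for beef FSCs.

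Followed as written, the plan leaves this clause of the primary hypothesis without an answer. A beef compound that behaves as hypothesised fails the validation rule. The only other signal is a non-significant change, which in 20 people is weak evidence of anything. FDR adjustment and measurement noise both make non-significance more common, so neither helps to separate stable compounds from unstable ones.

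**Working it through.** **1. The plan's own figure.** Sample size {14} gives N = 20 for 80% power at d = 0.45 (mean difference / SD of the difference) and alpha 0.05/21 = 0.0024, paired t-test. A noncentral-t calculation gives 10.4% power two-sided and 15.5% one-sided, so the figure does not reproduce. That is a separate matter and this point does not rest on it. No figure is given for stability.

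**2. What a stable beef FSC would do under the printed rule.** Let MB be mini-MED beef, MS mini-MED salmon and W Western. Suppose a compound follows beef intake and is equal on both backgrounds. Changes from baseline are left open, because they depend on earlier beef intake.

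| Order | Changes over mini-MED periods | Changes over Western periods |
|---|---|---|
| MB, W, MS, W | open; fall (W to MS) | none (MB to W); rise (MS to W) |
| MS, W, MB, W | open; none (W to MB) | rise (MS to W); none (MB to W) |
| W, MB, W, MS | none (W to MB); fall (W to MS) | open; none (MB to W) |
| W, MS, W, MB | fall (W to MS); none (W to MB) | open; rise (MS to W) |

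Apart from the first period, such a compound is flat or falling on mini-MED and flat or rising on Western. The rule asks for the reverse. Splitting by period does not help, because it keeps the same expected directions and does not contrast MB with W.

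**3. What a non-significant MB-versus-W difference would be worth.** Paired two-sided test, n = 20 completers (Sample size {14}). The 0.5 SD shift is an assumption, close to the protocol's minimum effect of 0.45. Miss rate = 1 − P(|T| > t(1−α/2; n−1)), where T is noncentral t with n − 1 = 19 degrees of freedom and noncentrality d√n = 0.5 × √20 = 2.24.

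| True shift | alpha 0.05 | 0.05/21 | 0.05/76 |
|---|---|---|---|
| 0.45 SD | 52% | 90% | 95% |
| 0.50 SD | 43.5% | 86% | 93% |

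The 76 is the number of beef compounds detected in plasma (Table 1). The Bonferroni columns only bracket what FDR would do. Simulating Benjamini-Hochberg at 5% over 76 independent compounds with a 0.5 SD shift gives a miss rate of about 60% if all shift, 84% if a quarter shift and 90% if a tenth shift. With all 22 enrolled, the 0.5 SD misses are 39% at 0.05 and 91.5% at 0.05/76.

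**4. Interval width.** The 95% half-width is t(0.975; 19)/√20 = 2.093/4.472 = 0.47 SD. An estimate of exactly zero would not exclude a shift of 0.45 SD.

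**5. What an equivalence criterion could deliver.** Two one-sided tests at 0.05 (90% interval inside the margin), true difference zero, n = 20, unadjusted. The pass rate is 25% at ±0.45 SD, 39% at ±0.5 SD, 89% at ±0.75 SD and 99% at ±1 SD. These use a single paired difference; averaging the two Western visits should improve them.

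**6. Why the margin should not be in units of the compound's own SD.** With a ±0.75 SD margin, a true 0.45 SD shift passes 36% of the time. For a fixed shift of 0.5 units, a margin of 0.75 times the SD passes 29% when the SD is 1 and 69% when it is 2, so the noisier compound passes more easily. With the margin held at 0.75 units, simulation gives a pass rate of about 4% when the SD is 2.

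**The case against.** A reader might infer that the trial will report beef compounds as stable because their change was not significant, and so pass noisy compounds as good biomarkers. The documents do not support that. Nowhere does the protocol say non-significance will be read as stability, and its only decision rule would class an unchanged or noisy beef FSC as not validated. This stands, and it is why the point is a mismatch and not a prediction of false claims.

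Stable and reproducible could also mean only that beef FSCs are found again on either background, which needs no margin. Background and rationale {6a} leans that way. But the printed analysis does not implement that reading either, since it expects decreases on Western, where beef is eaten.

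A margin might sit in an analysis plan that is not shown, and Trial design {8} calls the approach exploratory. A missing margin alone would indeed be no finding. Here, however, the article prints the primary analysis and its decision rule, and these conflict with the primary hypothesis for beef. The exploratory label lowers the stakes without resolving the conflict.

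It might also seem that only participants who move directly from mini-MED beef to Western are informative. That is not so: everyone who completes has one end-of-mini-MED-beef visit and two end-of-Western visits, so all 20 contribute.

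**Conclusion.** The point holds as a mismatch between the hypothesis and the printed analysis. No planned FSC analysis can support stability of beef FSCs across backgrounds: an unchanged beef compound fails the validation rule, and its non-significant change would not be evidence of stability. For scale, 20 completers miss a 0.5 SD shift about 44% of the time at 0.05, and about 60% to 90% under Benjamini-Hochberg in the scenarios tried.

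Those rates assume a paired two-sided test on one difference per person, normal differences, independent compounds for the FDR simulation, and a shift chosen for illustration. The mismatch itself depends on none of these. It should be resolved before the batch analyses, since it concerns part of the primary hypothesis.

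**What to change.** Add a separate analysis for beef FSCs. For each compound, estimate the within-person difference between the end-of-mini-MED-beef visit and the mean of the two end-of-Western visits, with a confidence interval (90% to match the calculation above), on the batch-corrected scale. Call the compound stable only if the interval lies inside a margin fixed before analysis. Set that margin in units that do not depend on the compound's own paired-difference SD, for example a fold change on the log2 scale or a fixed number of ranks. Otherwise report the estimate and interval as *not shown to be stable*. State that the significant-rise, significant-fall rule does not decide this clause for beef. The alternative is to drop the word stable from the hypothesis.

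The cost is a few sentences and a justified choice of margin, with no new visits or samples. The downside is that few beef compounds may be declared stable with 20 completers: at a margin equivalent to 0.45 SD, only about 25% of truly unchanged compounds would pass on a single paired difference.

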### Trial design {8}

This trial is a 16-week randomized, multi-intervention, semi-controlled feeding study of Mediterranean-amplified (mini-MED) and habitual/Western-style (Western) isocaloric dietary interventions containing 500 kcal/day from target foods. Participants are randomized (1:1) to start either the mini-MED or the Western dietary intervention, with subsequent assignment to the other upon completion of the first. Each 4-week intervention (mini-MED and Western) is repeated once. The Western intervention serves as both a washout of the mini-MED foods and a negative control for the postprandial response when the mini-MED foods are not consumed. Within the mini-MED arm, participants are further randomized to first receive salmon (mini-MED salmon) or lean, unprocessed beef (mini-MED beef) as a protein source, with consumption of the alternate protein source in their second mini-MED intervention period (Fig. 1). Outcome measures and biospecimen sampling take place at baseline and intervention weeks 4, 8, 12, and 16, and outcomes will be assessed using an exploratory approach.

